### Study Overview

This protocol is reported in accordance with the SPIRIT (Standard Protocol Items: Recommendations for Interventional Trials) 2025 guidelines for randomized trials, and any significant modifications to the protocol will require prior approval from the study sponsor. An overview of the study design is shown in Figure 1. A total of 210 participants will enroll in this randomized controlled clinical trial with a parallel-group design and equal allocation. All participants will receive a 12-month IDWL program, and those completing the 3-month assessment visit will be randomized to receive (1) a 9-month yoga program (YOGA; delivered during months 4‐12) or (2) a 9-month contact-matched control “Health & Wellness program” (WELLNESS; delivered during months 4‐12). The choice to delay randomization to YOGA or WELLNESS until after the 3-month assessment, rather than at baseline, was made to give participants time to build foundational WL skills without added burden and to reinforce self-regulatory skills at a time (3 months) when WL-related motivation may begin to dip [7,52]. Additional rationale to delay randomization to YOGA or WELLNESS is provided in the discussion. A full description of all intervention components is detailed below and conforms with the TiDieR (Template for Intervention Description and Replication) checklist for intervention reporting to enhance clarity and replicability.

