Yoga and wellness classes will be delivered via videoconferencing software (ie, Health Insurance Portability and Accountability Act [HIPAA]–compliant Zoom; Zoom Video Communications). There will be no intervention during months 13‐18. Randomization will occur at the 3-month assessment (ie, 3 months into the IDWL) in equal numbers based on a permuted block randomization procedure with small, random sized blocks, stratified by biological sex, racial or ethnic minority status, and percent WL achieved during the first 3 months of the WL program (<5% vs ≥5% WL). The randomization scheme was generated by the study statistician using R Studio (version 3.6.0) and uploaded into REDCap directly (to ensure study staff was kept blinded toward the full schematic). Participants will be recruited in cohorts over the study period. Assessments of weight, aerobic PA minutes, dietary lapses, potential lapse triggers (eg, affect, craving, and dietary temptations), and self-regulation mediator variables will be measured at baseline, 3 months (just prior to randomization), 6 months (mid-treatment), 12 months (postintervention), and 18 months (following a 6-month period of no intervention). At each assessment period, data will be collected via a series of REDCap questionnaires, an Actigraph accelerometer, and a 10-day EMA protocol (ie, 5 surveys per day over 10 days with each survey taking 2‐5 minutes to complete).

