### Data Analytic Plan and Sample Size Considerations

#### Sample Size Considerations

This study is fully powered for the primary aim, which is to examine treatment effects on WL from baseline through follow-up, taking into account the initial 3-month WL period. Power was calculated using a combination of G*Power and MPlus Monte Carlo estimation. Effect sizes were based on a preliminary study assessing the effects of yoga for WL that showed within the yoga condition, there was significant WL from 3 to 6 months (Cohen *d*=0.45). Effect sizes from both yoga and contact-matched control arms were used to estimate a between-group effect at follow-up to use in the power calculations (difference in median percent WL of 3.5% between conditions among those with high initial WL; 95% CI 0.005-0.139). Assuming a similar effect size, 20% correlation between covariates, a total sample size as low as 146 would yield sufficient power (>80%) for testing between-group effects on WL from baseline. However, the final sample size was inflated to 210 to account for (1) the possibility that the effect size estimates that were obtained from our pilot work and used to determine the sample size were not generalizable, (2) adequately powered secondary aims (secondary outcomes and mediation), and (3) attrition rates similar to what we have seen in past studies by this research team (<20% of randomized sample at the end of treatment).

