#### Missing Data

Analyses will be on the intent-to-treat sample (everyone randomized will be included in the final analysis) under various assumptions about the missing data mechanism. Sensitivity to these assumptions will be tested. Specifically, we will gather follow-up information and reasons for dropout regardless of protocol completion and censor at the point of loss. We will compare the robustness of our findings using 3 statistical approaches for handling missing data. First, we will use a multiple imputation approach to impute missing outcomes. Next, we will use inverse probability weighting with propensity scores. This is a two-step method: (1) using logistic regression, the probability of missingness is modeled as a function of baseline covariates and baseline values of the outcome and (2) the inverse of the propensity scores (predicted probabilities of dropout from the first step) serves as weights in our regression model of the outcomes. Provided the data are missing at random or that the probability of missingness can be fully explained by observable data, this approach produces asymptotically unbiased estimates. To allow for the possibility that the missing at random assumption may not hold, we will also use a third approach, pattern mixture models, in which the distribution of the outcome is assumed to follow a mixture of 2 distributions: one for those who complete follow-up and another for those who do not.

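### The inverse-probability weights are specified upside down: 1/P(dropout) is written where 1/P(observed) is needed, so the unbiasedness claimed for this sensitivity analysis does not hold

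*Protocol article*

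**What the plan says.** The Missing Data section names three approaches and gives their purpose: "We will compare the robustness of our findings using 3 statistical approaches for handling missing data". They are multiple imputation, inverse probability weighting and pattern mixture models. The weighting is described in two steps:

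- Step 1: "using logistic regression, the probability of missingness is modeled as a function of baseline covariates and baseline values of the outcome".
- Step 2: "the inverse of the propensity scores (predicted probabilities of dropout from the first step) serves as weights in our regression model of the outcomes".

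The section then states that, if data are missing at random or missingness is fully explained by observable data, "this approach produces asymptotically unbiased estimates".

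Both steps name missingness or dropout as the modelled event, and the parenthesis in step 2 defines the score explicitly. No other part of the article converts it to the probability of remaining under observation.

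**The concern.** Inverse probability weighting lets each completer stand in for similar participants who were lost. A completer of a type that often drops out must therefore count for more. Dividing by the probability of dropout does the reverse. It also makes the weights grow without limit as that probability approaches zero: at 5% dropout the weight as written is 1/0.05 = 20, against 1/0.95 = 1.05.

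The analysis exists to show whether the weight-loss result survives dropout. If it were coded as written, it could disagree with a sound primary result, or appear to confirm a distorted one, purely because of the formula.

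**Working it through.** The plan gives no figure for this analysis, so there is none to reproduce. The formula was tested directly.

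**Algebra.** Let p(x) be the probability of dropout given covariates x, and f(x) the covariate distribution of everyone randomized. The covariate distribution among participants in the weighted regression is proportional to:

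- no weights: f(x)(1 - p)
- weights 1/(1 - p): f(x), the randomized population
- weights 1/p, as written: f(x)(1 - p)/p, tilted further towards those least likely to drop out

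Only the second recovers the target. If p is constant, the weights are constant and do no harm.

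**Arm mean, exact two-stratum case.** From the protocol: attrition is expected to be "<20% of randomized sample at the end of treatment" (Sample Size Considerations); the example takes 20% overall, the upper end. Assumed: two strata of equal size, defined by a covariate in the missingness model, with mean 12-month changes of -8 and -2 kg, so the true mean is -5.00 kg. Dropout is 10% and 30%.

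- Completers: 0.5 x 0.90 = 0.45 and 0.5 x 0.70 = 0.35.
- Unweighted: (0.45 x -8 + 0.35 x -2)/0.80 = -5.375.
- Correct weights: 0.45/0.90 = 0.50 and 0.35/0.70 = 0.50, giving -5.00.
- As written: 0.45/0.10 = 4.50 and 0.35/0.30 = 1.167, giving (4.50 x -8 + 1.167 x -2)/5.667 = -6.76.

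| Dropout in the two strata | Unweighted | 1/(1 - p) | 1/p, as written |
|---|---|---|---|
| 15% / 25% | -5.19 | -5.00 | -5.92 |
| 10% / 30% | -5.375 | -5.00 | -6.76 |
| 5% / 35% | -5.56 | -5.00 | -7.47 |

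The bias as written is in the same direction as the unweighted bias and 4 to 5 times its size (for 10%/30%: 1.76/0.375 = 4.7).

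**Between-arm contrast, large-sample simulation.** N = 2,000,000, all inputs assumed. X is a standard normal prognostic covariate. Weight change is -5 + 3X plus, in YOGA, an effect of -2 (with +1X added where there is effect modification), residual SD 5. Log-odds of dropout are -1.6 plus 0.8X where dropout depends on X; overall dropout is 18% to 20%. Weights use the true p, which varies by arm in the two arm-specific rows. The true contrast is -2.0. Entries are unweighted / 1/(1 - p) / 1/p.

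| Scenario | Unadjusted | Adjusted for X |
|---|---|---|
| Same dropout in both arms, no effect modification | -2.0 / -2.0 / -2.0 | -2.0 / -2.0 / -2.0 |
| Same dropout, X modifies the effect | -2.14 / -2.00 / -2.78 | -2.13 / -1.99 / -2.78 |
| Dropout depends on X in YOGA only | -2.42 / -2.00 / -4.39 | -2.0 / -2.0 / -2.0 |
| Dropout depends on X in WELLNESS only | -1.58 / -2.00 / +0.39 | -2.0 / -2.0 / -2.0 |

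In these scenarios the effective sample size is 61% to 68% of completers with 1/p, against 97% to 99% with 1/(1 - p). In the first row the contrast is unbiased, but the WELLNESS mean is -7.39 with 1/p (true -5; unweighted -5.42).

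**The case against.** The strongest reply is that this is a drafting slip. The section names a standard method and claims its standard property, so the authors may well have meant 1/P(observed), and nothing shows that inverted weights will be programmed. That is fair as to intent. It does not rescue the text, which identifies the score as the probability of dropout.

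Three stronger readings are tempting, and the document does not support them.

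- **That the treatment contrast must be more biased than with no weighting.** The table shows it need not be. It also depends on what enters the missingness model. Suppose there is no treatment effect, dropout is 10%/30% in one arm and 20%/20% in the other, with the same -8/-2 kg changes. With arm in the model, the weights as written give a spurious difference of 6.76 - 5.00 = 1.76 kg, against 0.375 kg unweighted. With arm left out, "parallel-group design and equal allocation" makes the pooled dropout 15%/25%. The weights as written then give 6.09 - 5.75 = 0.34 kg, slightly less than unweighted, and correctly inverted weights from the same model give 0.376 kg. The article does not say whether arm is included.
- **That the primary result is compromised.** The Primary Aim section rests on a longitudinal mixed model that adjusts for initial weight loss and confounders. Weighting is one of three robustness approaches.
- **That the missingness model is wrong because it names only "the probability of missingness is modeled as a function of baseline covariates and baseline values of the outcome".** The full predictor list, any stabilisation and the imputation model are details an article commonly leaves to the analysis plan. The unbiasedness sentence is conditional on missingness being explained by the data used. A baseline-only model would be a limitation, not an error of statement.

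**Conclusion.** The weight is wrong as written. Even granting the section's own condition of missing at random, the stated formula does not give asymptotically unbiased estimates, except where dropout is unrelated to the covariates that drive outcome.

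When dropout depends on a prognostic covariate in the model, arm means move further from the truth than with no weighting: about -6.8 against -5.4 kg for a true -5.00 kg in the central example, and -5.9 to -7.5 kg over the range tried. The contrast is biased only under effect modification by the dropout predictor or arm-specific dropout; adjustment for the predictor removed the second source where there was no effect modification. Effect modification is a live possibility here, since the Introduction reports a pilot benefit among those with at least 5% initial loss and the Exploratory Aims list initial loss as a moderator. Otherwise the loss is precision.

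The means, effects and dropout splits are assumptions; the direction of the error in the weight is not. The consequence is confined to one sensitivity analysis.

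**What to change.** Reword step 2 to say that each observed outcome is weighted by 1/P(observed) = 1/(1 - predicted probability of dropout), with the weights applied to participants whose outcome is observed. Equivalently, model the probability of being observed in step 1 and keep the inverse in step 2. Check that the analysis plan and the code carry the same definition.

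The cost is one sentence and no new data. The Results section says that enrollment is ongoing, so the correction can be made before outcome data are analysed.

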## Results

This RCT was funded in July 2023 with an original project timeline of July 2023-June 2028. Enrollment began in February 2024 and is ongoing with the expectation of closing enrollment in June 2026. As of the submission of this protocol manuscript, recruitment timelines have been achieved, and 4 of 5 cohorts have launched. Upon study completion, results will be analyzed, and it is expected that the primary outcome findings will be submitted for publication within 6 months of the project end date.

## Discussion

### Principal Findings

This paper provides a summary of the rationale and methods of the PATH Trial. The primary goals of this randomized trial are to examine whether the addition of yoga to behavioral WL treatment improves long-term WL and to elucidate mechanisms through which yoga impacts weight in WL-seeking adults. These findings will have clinical relevance, as overweight and obesity are global health challenges linked to cardiometabolic risks, and despite effective WL interventions, long-term WL remains difficult [35,36]. Therefore, it is crucial to identify and test novel strategies, such as yoga, which have the potential to support sustained WL.

This study results from a synthesis of literature from a variety of disciplines using yoga interventions (cardiometabolic, pain, and addiction fields) and proposes a unique application of yoga to the area of weight management. While these other disciplines tend to focus on the psychological benefits of yoga for improving health, the weight control field has traditionally viewed yoga as a “mode” of exercise and has failed to consider that yoga is a mind-body intervention that could indirectly impact weight via psychological mechanisms (eg, improvements in self-regulation). Therefore, it is important to delineate that a yoga practice is not an exercise modality that produces effects similar to aerobic exercise, which has a higher caloric expenditure and is commonly recommended in WL programs, and therefore will be unlikely to elicit a comparable exercise-induced energy deficit [69]. Unlike past literature, this trial is uniquely designed and fully powered to evaluate self-regulatory pathways through which yoga impacts dietary lapses and WL, representing the first RCT to examine these mechanistic pathways within the context of WL treatment.

This design was chosen as the best method of answering the questions central to the study. For example, the use of an equal contact-time wellness program for the control arm, delivered through the same live, synchronous videoconferencing modality as yoga, provides a stringent test of the relative efficacy of yoga as a complementary therapy to IDWL. The decision to implement yoga at the start of week 14, rather than week 1, was made so that participants can dedicate their focus to initiating important WL skills and achieving program goals at the start of the program (eg, regular self-weighing, self-monitoring, calorie restriction, and aerobic exercise). Adding yoga at week 1 would further increase participant burden, which is already high at this time. Delaying yoga until week 14 allows additional time for these important WL skills to become more routine, which then allows individuals more time to dedicate to practicing yoga. Further, given that maximal WL in IDWL programs is achieved around 3 months [7,52] (earlier than what is observed with in-person treatment [35]), one way to bolster WL at this time would be to add an intervention component, which can both add novelty and strengthen self-regulation. Research supports this approach, as individuals report that over time, boredom increases; it requires more effort to stay on track, and the cost-benefit ratio for WL increases (ie, the effort required to adhere to WL practices is greater than the positive feedback received for adherence) [35,70-74]. This makes continued diligence to self-regulatory WL behaviors challenging, particularly during times of high stress, emotional difficulties, or when exposed to highly palatable foods. Our pilot study, which also implemented yoga following a period of WL treatment, provided further support for this decision [51].

This study is novel, in that it is one of a handful of studies to combine yoga with a WL program, and it is the first to empirically examine this combination of approaches using fully remote intervention procedures (ie, IDWL combined with live, online yoga classes). We made the decision to combine yoga with IDWL treatment from months 4 to 12 (vs stopping IDWL treatment) for the following reasons. First, most WL programs are 1 year in duration, and there is no added cost to continuing the IDWL program, given that it is fully automated. Additionally, as prior research suggests that yoga reinforces self-regulatory skills taught within IDWL, extending the IDWL treatment would provide an opportunity for participants to “practice” these skills. Finally, this approach allows for examination of the combined effect of yoga and IDWL.

Another novel aspect of this study is the use of technology-based assessment methods (EMA) for capturing participants’ dietary lapses and potential lapse triggers (eg, cravings, temptations, and affect) in near-real-time, within a naturalistic setting, while participating in a WL and yoga intervention. We also pair these survey assessment methods with objective monitoring of aerobic PA, so that they occur simultaneously. While pilot work indicates that yoga participation does not reduce aerobic exercise engagement [4], this is a frequent concern regarding the inclusion of yoga into a WL program. Thus, this study will be able to empirically answer whether including yoga reduces engagement in other modalities of exercise while also allowing for novel exploratory analyses related to both the acute and chronic effects of yoga on psychological and dietary variables.

This study will also add to the literature in its ability to examine for whom yoga is most efficacious for producing WL. Examination of yoga within the context of a weight management program is in its infancy, and studies assessing the effect of yoga on body weight have been primarily in the normal weight, non-Hispanic, White female population. This study seeks to enroll ≥35% male individuals and ≥40% individuals from racial and ethnic groups that are commonly underrepresented in WL trials. Thus, we will be in a unique position to explore whether the effect of yoga on WL differs by biological sex and race or ethnicity or whether there are other significant moderators (eg, BMI, 3-month WL, and socioeconomic status) of the effects of yoga on WL. To our knowledge, this is the first study to examine whether there are specific subgroups of WL-seeking individuals who benefit most from yoga participation.

### Conclusions

The proposed study is significant because it is one of the few trials to examine the combined effect of yoga and WL treatment among individuals with overweight or obesity and the first fully powered trial to assess the combination of yoga and WL beyond 6 months. While the yoga field is often criticized for a lack of scientific rigor, this study represents a significant step toward improving the quality of research in this area, as it is empirically guided and thoughtfully designed to ensure rigor and reproducibility of study findings (eg, randomized trial with contact-matched control, manualized protocols, and fidelity checks). This study also uses and tests an easily disseminated intervention model, which combines a fully automated, low-cost IDWL program with live, online yoga classes; thus, translation potential is high. Examination of mediators and moderators of the effect of yoga on WL is also important for improving theoretical models of yoga and self-regulation, optimizing future intervention trials, and enhancing our understanding of how and for whom yoga impacts long-term WL. Ultimately, if primary hypotheses are confirmed, yoga could be considered a valuable intervention component for improving IDWL treatment. In the future, if favorable results are observed, longer-term follow-up would also be warranted to better understand the role of yoga in WL maintenance over periods of time longer than this study is planning. This study has great potential to make a significant contribution to both yoga and WL fields and addresses critical gaps in the current literature.
